### Sample size {14}

The sample size is based on the primary outcome—the proportion of participants showing remission defined as a DAS-28-CRP < 2.6, 24 weeks from randomisation. A survey of 33 rheumatologists in June 2020 indicated that 13 (39%) and 29 (89%) would prescribe subcutaneous methotrexate if it increased remission by 15% or 20%, respectively. Given this marked difference, the trial was powered to detect an absolute difference of 17.5% between oral and subcutaneous methotrexate. Assuming that 30% of participants in the oral methotrexate arm were in remission at week 24 [14], 173 participants would be required in each arm to detect a difference of 17.5% (i.e. 47.5% of participants in the subcutaneous arm in remission), with 90% power, and a 2-sided alpha of = 5%. Assuming 10% loss to follow-up at 24 weeks, 386 participants should be randomised. Since the primary objective of the trial is to assess the relative effectiveness of first-line subcutaneous versus oral methotrexate, the primary comparison will be as randomised (i.e. intention to treat). Therefore, no additional adjustments to the sample size are necessary. Power calculations were performed using PASS v12 (NCSS).

### Recruitment {15}

Strategies to promote the trial include a poster for use in clinic areas and a postcard to hand out to any interested parties. A trial website will contain information for both patients and recruiting staff, including regular updates on recruitment figures.

At the initial presentation visit to the rheumatology clinic, potential participants will be given the PIS. Site staff will have the opportunity to post or email a PIS to patients who were not approached in the clinic. They will also be able to make a telephone call to the patient to discuss the trial and gauge interest.

Participants will be offered two £25 vouchers as a thank you for their involvement and to help cover any additional transport costs they may experience. These will be given after baseline and 24-week visits.

Sites randomised to SWAT intervention group 1 will use the video PIS, which has a QR code link to an information video, showing the trial in animated format, and a nurse demonstration of using the subcutaneous methotrexate injection device. At the interim analysis stage, if there is sufficient evidence of a difference in consent rates between the two SWAT arms in favour of the SWAT intervention, the video SWAT will be rolled out across all sites with the aim of improving recruitment across sites.

Site recruitment targets will be set according to size and capacity of the local team. Recruitment will not be capped; and all involved NHS trusts will be given the opportunity to over recruit up to the point of the overall target recruitment figure of 386 being met. The MOOSE patient advisory group, consisting of RA patients and/or carers will be involved at key stages throughout the trial, including contribution to the development of recruitment strategies, data collection and retention. Scheduled meetings will take place, but there will also be capacity to meet on an ad-hoc basis as-and-when issues with recruitment arise.

## Assignment of interventions: allocation

### Sequence generation {16a}

Eligible patients who consent will be allocated to receive either subcutaneous methotrexate or oral methotrexate on a 1:1 ratio. Treatment will be assigned randomly using a minimisation algorithm balancing by trial recruiting centre, DAS-28-CRP (< 5.1 and ≥ 5.1) and disease duration (< 4 months, 4–12 months, and > 12 months). These variables are selected due to their likely association with the primary outcome.

### Concealment mechanism {16b}

Allocation will be concealed using a web-based randomisation system developed and maintained by the Nottingham Clinical Trials Unit (NCTU) and hosted on a secure server, accessed via a secure website.

### Implementation {16c}

The site Principal Investigator (PI), PI delegate or research nurse conducting the patient visit will enrol the participant on the MOOSE Research Electronic Data Capture (REDCap) database system. Randomisation is integrated within the REDCap database. When all baseline data has been completed, and randomisation requested, the database provides details of treatment allocation on the randomisation form.

## Assignment of interventions: blinding

### Who will be blinded {17a}

Interventions are open-label therefore participants and their care providers including rheumatologist will not be blinded to the treatment allocation. Disease activity (DAS-28-CRP) assessors will be blinded to the treatment allocation throughout the trial. This may be a research or usual care team member. The trial statistician will be blinded and will not have access to individual participant data until after the database has been locked. Adherence to allocated treatment will be provided by an unblinded independent statistician, who will also provide any unblinded disaggregated data for the DMC. The TSC will be blinded to treatment allocation unless specifically recommended by the DMC. The qualitative researchers will not be blinded to the participants route of methotrexate allocation.

The Chief Investigator (CI) will be partially blinded, only having access to the unblinded data for participants randomised at their site, or where serious adverse event (SAE) review is determined to be related to the trial treatment. The TMG will be partially blinded to treatment allocation, with only the trial management and data management staff having access to participant data that may be unblinding.

### Procedure for unblinding if needed {17b}

Only researchers assessing disease activity (DAS-28-CRP) will be blinded to treatment allocation. Interventions will be open-label and both participants and research clinicians will be aware of the treatment allocation; therefore, there is no requirement for blind-breaking procedures.

## Data collection and management

### Plans for assessment and collection of outcomes {18a}

Trial outcome data from clinic visits will be collected in the REDCap database. Site staff will enter baseline data and assessments, and follow-up assessment data directly into REDCap. Blinded assessment data is collected on a paper CRF and later transcribed to the eCRF by an unblinded member of the research team. Participant questionnaires at weeks 4 and 8 are either entered directly to the database by participants who receive an individual link by email, or by post if preferred and transcribed to the eCRF by NCTU staff.

Qualitative data collection will involve semi-structured interviews in both arms. Maximum variance sampling will ensure patient diversity e.g. age, gender, ethnicity, health literacy, perceptions of acceptability. We aim to interview approximately 10 participants in each arm, depending on data saturation. All those interviewed at 4–8 weeks will be invited to another interview between 24 and 32 weeks.

### Plans to promote participant retention and complete follow-up {18b}

Participant research visits have been aligned where possible to coincide with standard care clinic visits so as not to burden the participant with additional clinic visits. Discussions with the study’s public co-applicant (MB) and our Patient Advisory Group has informed our plans to promote participant retention and follow-up. DAS-28-CRP assessments are in line with usual care, and participants are requested to complete the patient-reported outcome questionnaires whilst in clinic. Follow-up is continued regardless of whether the participant is adherent to trial intervention and is encouraged by reiterating the importance of the follow-up visit both to site staff and participants, by sending monthly newsletters to site staff and quarterly participant newsletters. The week 24 visit is an additional research visit, and at this time point participants receive a £25 voucher. Participants who wish to discontinue are given the option to partially remain in the study. This may be in the form of attending some, but not all, follow-up visits or by completing fewer questionnaires. All data collected before discontinuation will remain in the study.

Text messages and email reminders will be sent to participants to prompt them to complete the 4 and 8 week questionnaires, followed by a telephone call if required.

### Data management {19}

The Data Management Plan (DMP) will include the agreed validation specification, roles and responsibilities for the trial data and user access. The trial database, REDCap, is a validated secure web-based platform which allows for data tracking via date stamped audit logs. MOOSE participants will be identified on REDCap only by a unique participant identifier (their trial/participant ID) to protect from bias and ensure confidentiality.

Measures to improve data quality include warnings flagging database entries that are outside of the protocol parameters, for outcome measures including DAS-28-CRP components. Data reported on each eCRF will be checked for missing data or discrepancies. Decisions on how to treat anomalous data will be made by members of the TMG blinded to allocations and documented in the DMP and/or Statistical Analysis Plan (SAP); where required.

#### Qualitative data management

The contact details of those willing to participate in the interview study will be shared with the qualitative researcher at Keele University. The interview will be digitally audio/video-recorded, according to participant preference, and the digital file saved with the interview recordings and labelled with the participants’ unique ID number. The recordings will be shared securely with an approved transcription company for the purposes of transcription. Data will be held on Keele University’s secure data servers. Access to the MOOSE qualitative data will be restricted to named authorised individuals.

### Confidentiality {27}

All trial staff and investigators will endeavour to protect the rights of the trial’s participants to privacy and informed consent, and will adhere to the Data Protection Act, 2018. The CRF will only collect the minimum required information for the purposes of the trial. Access to the CRF will be limited to the trial staff and investigators and relevant regulatory authorities. Participant data will be held securely and password protected, with access restricted by user identifiers. Identifiable information will be stored within a restricted channel of the REDCap database, and limited access allowed for the purpose of questionnaire and treatment acceptability interview communication. Information about the trial in the participant’s medical records will be treated confidentially in the same way as all other confidential medical information.

Individual participant medical information obtained as a result of this trial are considered confidential and disclosure to third parties is prohibited except for the need to disclose such medical information to the participant’s medical team and appropriate medical personnel responsible for the participant’s welfare. If information is disclosed during the trial that could pose a risk of harm to the participant or others, the researcher will discuss this with the CI and where appropriate report accordingly.

Data generated as a result of this trial will be available for inspection on request by the participating physicians, the University of Nottingham representatives, the Research Ethics Committee (REC), local NHS R&D departments and the regulatory authorities.

### Plans for collection, laboratory evaluation and storage of biological specimens for genetic or molecular analysis in this trial/future use {33}

All blood tests, including those taken at standard care clinic visits, and those taken at research visits, will be labelled, analysed and destroyed as per the local NHS hospital policy.

## Statistical methods

### Statistical methods for primary and secondary outcomes {20a}

The analysis and presentation of the trial results will be in accordance with the CONSORT guidelines and a full SAP will be developed prior to database lock. The primary objective of the trial is to determine the effectiveness of first-line subcutaneous versus oral methotrexate and as such, the principal approach to our primary comparative analysis will be to analyse as randomised without imputation of missing data, with due emphasis being placed on the confidence intervals for the between arm comparisons. Sensitivity and secondary analyses will be considered supportive to the primary. Characteristics and baseline data of randomised participants in the two trial arms at baseline will be described, using appropriate descriptive statistics.

The evaluation of the primary outcome will be performed using a mixed effects model for binary outcomes that includes study centre and disease duration as per the minimisation, and baseline DAS-28-CRP calculated using the CRP value obtained on the day of randomisation.

The primary estimands comparing the proportion of participants in remission at 24 weeks between those randomised to first-line subcutaneous methotrexate and first-line oral methotrexate, regardless of whether participants do not take or discontinue assigned treatment, or start a new treatment as add on or replacement therapy, will be the adjusted risk difference and 95% confidence interval.

#### Definition of populations analysed

Intention to treat dataset: All randomised participants are summarised/analysed according to their randomised treatment irrespective of the treatment(s) they received. This is the primary dataset to be used in both the effectiveness and the safety analyses.

Safety dataset: All randomised participants are summarised according to the treatment they receive, irrespective of their randomised allocation. This dataset may be used for sensitivity analyses.

Secondary outcomes will be analysed using appropriate regression models that include site and disease duration as recorded for minimisation, and DAS-28-CRP calculated using all components as collected at baseline, and baseline values of that outcome if measured and will be as randomised without imputation of missing data, unless otherwise indicated in the SAP.

### Interim analyses {21b}

No formal interim analyses are planned for the main trial. A feasibility assessment has been built into the trial in the form of an internal pilot phase examining recruitment and retention. The stop–go criteria (shown in Table 3 below) will be used to determine the progression of the trial recruitment 9 and 15 months after the first participant is randomised. Recruitment will be assessed against the overall recruitment target at 9 and 15 months. Retention will be reviewed at 15 months and a decision made based on the proportion of participants who have withdrawn from the trial (trial follow-up not allocated treatment) at or before the 24 week follow-up visit. The above criteria to aid decision making about progression of the trial has been proposed by the trial team and agreed with the TMG, and funder (NIHR). The final agreement on whether the trial should stop or continue will take place after discussion with NIHR. Adherence to methotrexate route of administration will not form part of the progression criteria for the trial since this is a pragmatic treat to target protocol but will be regularly monitored by the TMG.

**Table 3 Tab3:**
[figure not shown]
Recruitment and retention progression guidance for internal pilot

#### MOOSE stop/go criteria

The MOOSE stop/go criteria is shown in Table 3.

The SWAT interim analysis to compare the proportions of participants consenting in the two intervention groups (those with PISs with the QR code to the information video and those with PISs which do not have the QR code) will be performed at 9 and then potentially at 15 months after the first participant is randomised to determine whether there is a greater proportion consenting in either of the intervention groups.

Where there is a notable difference in consent rates (as defined in the SWAT SAP) at 9 months, the PIS which is associated with the higher consent rate will be adopted for the remainder of the trial. If there is no difference, an additional interim analysis will be performed at 15 months. If a notable difference is observed at this point, the PIS which is associated with the higher consent rate will be adopted for the remainder of the trial. Where no notable difference is observed, both PISs will be used until the end of the trial.

### Methods for additional analyses (e.g. subgroup analyses) {20b}

The comparison of first-line subcutaneous and oral methotrexate on the primary outcome only will be performed in subgroups according to disease duration (less-than 4 months, 4–12 months, and more than 12 months), auto-antibody status (only RF positive, only anti-CCP positive, dual sero-positive, seronegative), body mass index (≥ 30 vs. < 30 kg/m2) and smoking status (current-smoker vs. not-currently smoking at the screening visit). The interpretation of any subgroup effect will be based on interaction tests (i.e. evidence of differential treatment effects in the different subgroups). It is acknowledged that these investigations will not be adequately powered.

Treatment acceptability interviews will be transcribed verbatim and analysed thematically using a framework approach [15, 16]. Following data familiarisation, a thematic framework will be developed using inductive and deductive coding [16]. For longitudinal analysis, summaries of each participant’s data [17, 18] will be used to identify perceptions of changes in acceptability of interventions and influences of change within case (each person) and in each intervention group (cross-case). Using the Beliefs about Medicines Questionnaire, a Necessity-Concerns Differential will be calculated. This score will provide a numerical indicator of how participants judge their personal need for different formulations of methotrexate relative to their concerns about the potential negative effects of taking methotrexate. Interpretation of data will be discussed with the patient advisory group and with researchers from different professional backgrounds (e.g. rheumatology, health services research), improving the trustworthiness of analysis [16, 19].

For the health economic analysis, both the during trial and future extrapolation models, the incremental cost-effectiveness ratio (ICER) estimated from probabilistic analyses will be calculated following guidance published by NICE [13]. The uncertainty in these ICERs will be explored, using seemingly unrelated regression for the first model [20] and for the second by estimating the confidence interval in the calculated ICERs presented, alongside an estimate in the true underlying uncertainty using a percentile approach [21]. To visualise the uncertainty, cost-effectiveness planes and cost-effectiveness acceptability curves will be provided. Comprehensive scenario/sensitivity analyses will be undertaken to explore the robustness of the results to changes in the values of key parameters (such as the projected use of biologic disease modifying anti-rheumatic drugs (e.g. anti-TNF agents), requirement for surgery and utility values for patients) to alternative plausible values, and by the inclusion of monetised values for absenteeism and presenteeism. If appropriate, value of information analyses will be conducted to show whether there is an incentive to collect further information, and on which parameters [22, 23]. The results from the value of information analyses will indicate the maximum cost of research to reduce decision uncertainty and will indicate whether further research would be seen as cost-effective.

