## Introduction

### Background and rationale {6a}

Rheumatoid arthritis (RA) is an inflammatory disease that most commonly affects the small joints of the hands and feet, causing considerable pain and functional impairment. It is a systemic disease and can cause a wide range of complications for patients, carers, the NHS and society. RA affects 0.7% of adults in the UK and can cause permanent joint damage and disability if not treated aggressively [1, 2]. Oral weekly methotrexate (≤ 25/week) has emerged as the first-line disease modifying anti rheumatic drug (DMARD) for the management of RA, with the proportion of patients treated with methotrexate increasing over time [3]. Self-administered subcutaneous injections are often used if there is gastrointestinal intolerance or suboptimal efficacy. According to our June 2020 survey of 33 UK rheumatologists, 14% offer methotrexate injections as a first-line treatment. Existing randomised controlled trials (RCTs) have suggested that first-line subcutaneous methotrexate has greater efficacy than first-line oral methotrexate [4–7], but these RCTs used a fixed dose of methotrexate, and did not employ a treat-to-target strategy with dose escalation of other drugs, as recommended in the National Institute for Health and Care Excellence (NICE) guidelines for the management of RA [4, 5]. Pharmacokinetic evidence supports the suggestion that subcutaneous methotrexate has greater efficacy, showing a plateau in bioavailability of oral methotrexate at doses > 15 mg/week, unlike for subcutaneous methotrexate [8]. A Canadian cohort study reported better control of disease activity with subcutaneous methotrexate compared to oral methotrexate but there was a large imbalance in starting dose, with 87% of participants starting subcutaneous methotrexate at 20–25 mg/week, whilst only 41% started oral methotrexate at these doses [9]. However, sub-cutaneous methotrexate can be painful to administer and cumbersome and are more expensive (£16.06 vs £0.75 for the 20 mg/week dose as per the British National Formulary (BNF) [10]. Cost-effectiveness analysis was not included in these studies. Evidence on effectiveness, tolerability and cost-effectiveness is required before injections can be recommended as a first-line treatment by NICE and British Society for Rheumatology (BSR).

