A mathematical model will be developed to estimate the cost-effectiveness of subcutaneous methotrexate compared with oral methotrexate. The model will take account of the results observed in the pragmatic trial, particularly those associated with costs to the NHS, EQ-5D-5L values, discontinuation rates and remission rates. The analyses will be in line with the NICE reference case, estimating a cost per quality-adjusted life year (QALY) gained for the more efficacious treatment from a probabilistic analysis [13].

The SWAT primary outcome will be the proportion of patients given a PIS who are consented at each site. Secondary outcomes include the proportion of participants providing primary outcome data (at 24 weeks), and the proportion of participants remaining in the trials at 52 weeks.

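### The extrapolation model's uncertainty is to be given as a percentile interval on the ICER, which cannot be interpreted if draws of the QALY difference straddle zero

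*Protocol article*

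**What the plan says.** The health economic paragraph of Methods for additional analyses {20b} plans ICERs for two models and treats their uncertainty differently.

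- **During-trial model:** uncertainty is explored "using seemingly unrelated regression for the first model".
- **Extrapolation model:** uncertainty is explored "by estimating the confidence interval in the calculated ICERs presented, alongside an estimate in the true underlying uncertainty using a percentile approach".
- **Displays:** the next sentence adds that "To visualise the uncertainty, cost-effectiveness planes and cost-effectiveness acceptability curves will be provided".
- **Value of information**, if appropriate: "The results from the value of information analyses will indicate the maximum cost of research to reduce decision uncertainty".

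The cost-effectiveness paragraph in Outcomes {12} (printed under the Safety outcomes subheading) names the comparison as subcutaneous against oral methotrexate. It then describes the result as "estimating a cost per quality-adjusted life year (QALY) gained for the more efficacious treatment from a probabilistic analysis". Neither place mentions net monetary benefit, or says how an ICER interval would be reported if simulated QALY differences took both signs.

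**The concern.** An ICER is a ratio, and ordering a set of ratios makes sense only if the denominator keeps one sign. A negative ICER arises both when subcutaneous treatment is cheaper and better and when it is dearer and worse, and the number alone does not say which. Draws with a QALY difference near zero give very large values of either sign. A 2.5 to 97.5 percentile range of such draws can have a negative lower limit that looks favourable but consists of the least favourable draws.

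A QALY difference near zero is plausible in this trial. One drug is compared by two routes under treat-to-target care, either arm may change route or move to another DMARD, the analysis is as randomised, and the sample size was set for remission and not for QALYs. Cost-effectiveness is part of the stated aim, so the numerical statement of its uncertainty should be readable whichever way the results fall.

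**Working it through.** **Plan figures.** The article states no ICER, QALY difference, QALY SD or cost SD, so there is no plan figure on this point to reproduce. Two plan figures serve as inputs.

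- *Patients per arm: 173* (Sample size {14}). This reproduces. The inputs are "Assuming that 30% of participants in the oral methotrexate arm were in remission at week 24" and "47.5% of participants in the subcutaneous arm in remission", two-sided 5% and 90% power. The two-proportion formula gives 161 per arm, or 173 with continuity correction. Allowing for 10% loss, 173/0.9 = 192.2, so 193 per arm and 386 in total.
- *Drug price* (Background {6a}): "16.06 vs £0.75 for the 20 mg/week dose", in pounds. Reading these as prices per weekly dose (an assumption), the yearly difference is 52 × (16.06 − 0.75) = £796.

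**Assumptions not in the documents.** QALY SD 0.15 to 0.25; cost SD £2,000; no correlation between costs and QALYs; normal draws; thresholds of £20,000 and £30,000 per QALY. These describe a 52-week within-trial comparison. They show the mechanism and do not forecast the extrapolation model.

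**Step 1: how often the denominator changes sign.** With d the true QALY difference and SE its standard error, P(difference ≤ 0) = Φ(−d/SE). This depends only on d/SE, so it applies to either model: 15.9% at d/SE = 1, 2.5% at 1.96, 0.1% at 3. For the illustration SE = SD × √(2/173) = SD × 0.1075, which is 0.0161, 0.0215 and 0.0269 for SD 0.15, 0.20 and 0.25. Over gains of 0.01 to 0.02, the share at or below zero runs from 10.7% (0.02, SD 0.15) to 35.5% (0.01, SD 0.25).

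**Step 2: what the percentile interval does.** Draws of cost/QALY were sorted and the 2.5 and 97.5 percentiles read off (400,000 draws). The Fieller interval for the same ratio is shown beside it; it is bounded only if d exceeds 1.96 SE.

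| QALY SD | True gain | Share ≤ 0 | Percentile interval (£) | Fieller (£) |
|---|---|---|---|---|
| 0.20 | 0.02 | 17.6% | −363,700 to 401,201 | unbounded |
| 0.15 | 0.03 | 3.2% | −75,849 to 183,083 | unbounded |
| 0.25 | 0.05 | 3.2% | −45,771 to 109,623 | unbounded |
| 0.20 | 0.05 | 1.0% | 5,344 to 74,370 | 6,064 to 103,968 |
| 0.25 | 0.07 | 0.5% | 4,277 to 43,123 | 4,474 to 47,994 |
| 0.20 | 0.07 | 0.1% | 4,700 to 30,746 | 4,716 to 30,967 |

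In the first row almost no draws are cheaper and better (under 0.1%), because the assumed cost difference is 796/215 = 3.7 standard errors above zero (cost SE = 2,000 × 0.1075 = £215). The negative lower tail is therefore made of dearer-and-worse draws. In the fourth row the 1% of such draws still pulls the upper limit from about £104,000 down to £74,000, since they are counted at the favourable end. By the last row the two methods agree.

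**Step 3: the alternative on the first row.** Incremental net monetary benefit at threshold λ is λ × d − cost.

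- At £20,000: 20,000 × 0.02 − 796 = −£396.
- SE = √((20,000 × 0.0215)² + 215²) = £481.
- 95% interval: −396 ± 1.96 × 481, or −£1,339 to £546.
- Probability of positive benefit: Φ(−396/481) = 0.21; by the same formula at £30,000, 0.39.

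These stay defined where the ratio interval does not. The two probabilities are points on the acceptability curve already planned.

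**The case against.** Much can be said for the plan, and most of it stands.

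- **Scope.** The ratio interval is planned only for the extrapolation model. The figures above use within-trial inputs, so they do not measure the problem in the model where the interval will be used. This stands.
- **Conditionality.** At a gain of 0.07 the interval is well behaved over the whole assumed SD range. The article gives nothing from which to say where the QALY difference will lie. This stands.
- **Existing displays.** A reader might infer that decision uncertainty rests on the ICER interval alone. The text does not support that: planes separate the quadrants, acceptability curves are defined in all of them, and decision uncertainty is tied to value of information analysis. They do not, however, put a readable interval in place of the one on the ratio.
- **Meaning of the terms.** The text distinguishes the confidence interval from the true underlying uncertainty, so the former may be simulation error. The source cited for the percentile approach is not at hand, and it may deal with quadrants. The objection therefore falls on the percentile approach as the article words it.
- **Direction.** A reader might infer that the sign of the contrast is left to the data. But Outcomes {12} names subcutaneous compared with oral, and the phrase about the more efficacious treatment may only describe how the ratio is expressed.
- **Detail left elsewhere.** A full protocol or health economics plan may say more. Against this, the ratio interval is a method the article states, not one it omits.

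**Conclusion.** The point holds as a minor one. For the extrapolation model the article commits the numerical statement of underlying uncertainty to percentiles of a ratio, with no provision for QALY draws on both sides of zero. Once more than about 2.5% of draws are at or below zero (d/SE under 1.96) and the cost difference is clearly positive, the lower limit itself comes from dearer-and-worse draws. Under the assumed inputs with SD 0.20 this covers gains below about 0.042 (1.96 × 0.0215); for SD 0.15 and 0.25 the boundary is about 0.032 and 0.053. Above it the interval recovers, fully so at d/SE of about 3.

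These boundaries rest on assumed SDs and within-trial numbers, so they illustrate the problem and do not predict it. The documents do not support the stronger reading that the planned economic analysis has no valid account of uncertainty: the planes, the acceptability curves and the seemingly unrelated regression are unaffected.

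**What to change.** In the health economics analysis plan:

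1. Define every increment as subcutaneous minus oral, whichever arm does better.
2. For both models, report incremental costs, incremental QALYs and incremental net monetary benefit with 95% intervals, at NICE thresholds named in advance.
3. Give the ICER as a point estimate. Add an interval only when essentially all QALY-difference draws share one sign, with the required share fixed beforehand. The 1% row in the table suggests setting it stricter than 99%.
4. If the confidence interval is meant as simulation error, say so; it can be given on net benefit.
5. Keep the planes and acceptability curves as planned.

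The cost is wording and slightly more reporting. The same draws are used and no new data are needed. The one loss is that some scenarios will carry no ICER interval.
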